**Fig. 3 Fig3:**
[figure not shown]
Flow diagram

**Fig. 4 Fig4:**
[figure not shown]
Study timeline

### Adverse events

All adverse events (AE) will be recorded in the hospital notes in the first instance. A record of all AEs, whether related or unrelated to the treatment will also be kept in the CRF. If the Investigator suspects that the disease or condition has progressed faster due to the intervention, then he will report this as an unexpected adverse event to the sponsor. Only deaths that are assessed to be caused by the trial intervention will be reported to the Sponsor. This report will be immediate.

Considering the safety profile of the interventions applied in this study (PGDT protocols that showed a benefit to reduce postoperative complication rate without significant adverse effects), we believe that institution of a safety committee is not mandatory.

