### Protocol a

Patients allocated to protocol A will received a GDT protocol based on dynamic parameters of fluid-responsiveness for optimization of fluid status (Fig. 1). Dobutamine will be used with discretion of the attending anesthesiologist as clinically needed. The protocol will be continued postoperatively up to 6 h when dynamic parameters remain applicable (controlled mechanical ventilation, absence of arrythmia, etc.). On the other hand, fluid challenge technique with 250 ml of crystalloid over 5 min will be used for fluid optimization considering 10% increase in CO as positive response.

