### Data collection

At randomization, demographic and clinical data will be recorded:
Age, sex, weight, heightAdmission diagnosisComorbidities (e.g. diabetes mellitus, chronic kidney injury, chronic obstructive pulmonary disease, cardiac dysfunction, etc.)

During perioperative period, main clinical parameters will be recorded:
Ventilation modality and parameters (spontaneous, assisted/controlled, tidal volume, respiratory rate, airway pressures, FiO_2_)Anesthetic/analgesic drugsHemodynamic parameters (blood pressure, heart rate, CO, SV, SVR, PPV, SVV)Arterial blood gasCentral venous blood gasFluids (crystalloids and colloids), transfusion and fluid balanceInotropic/vasoactive drugsDaily SOFA score

Finally, the following outcomes will be recorded:
Complication during hospital stay (Table 1)Hospital length of stayMortality at day 28

**Table 1 Tab1:** Complications assessed during postoperative period

Acute myocardial ischemia/infarction	Multiorgan failure
Cardiac arrhythmia	Delirium/psychosis
Cardiac/respiratory arrest	Urinary tract infection
Cardiogenic pulmonary edema	Bacteremia
Pulmonary embolism	Surgical site infection
Acute respiratory distress syndrome	Nosocomial pneumonia
Gastrointestinal bleeding	Unknow origin infection
Intestinal infarction	Stroke
Anastomotic leakage	Post-operative hemorrhage
Paralytic ileum	Surgical re-intervention
Acute kidney injury	

Severity of postoperative complications will be defined according to Clavien-Dindo classification [13]. Complication grades I and II will be considered as minor complications while grades III and IV will be considered as major ones.

The Case Report Forms (CRFs) will not bear the participant’s name or other directly identifiable data. The participant’s trial Identification Number (ID) only, will be used for identification.

The flow diagram according to CONSORT guidelines [14] is provided as Fig. 3. Figure 4 shows an overview of all outcome measures in accordance with SPIRIT guidelines [11].

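### The rule for reporting non-fatal events to the sponsor is keyed to disease progression, which does not fit this trial, so serious non-fatal events attributed to the protocol have no stated timely route

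*Protocol article*

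**What the plan says.** The Adverse events section of the protocol article sets out recording and reporting separately.

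- **Recording.** "All adverse events (AE) will be recorded in the hospital notes in the first instance", and "A record of all AEs, whether related or unrelated to the treatment will also be kept in the CRF". Recording is therefore complete and does not depend on relatedness.
- **Reporting, first trigger.** "If the Investigator suspects that the disease or condition has progressed faster due to the intervention, then he will report this as an unexpected adverse". That report is addressed to the sponsor.
- **Reporting, second trigger.** "Only deaths that are assessed to be caused by the trial intervention will be reported to the Sponsor". The next sentence adds: "This report will be immediate".
- **Oversight.** Citing the safety profile of the two protocols, the section concludes: "we believe that institution of a safety committee is not mandatory".

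Two other parts of the article bear on this. Data collection (Table 1) lists the 21 complications recorded as outcomes, among them "Cardiogenic pulmonary edema", arrhythmia, myocardial ischaemia and acute kidney injury, and has their severity graded by Clavien-Dindo. Statistical analysis plans one interim analysis by an independent statistician at 100 recruited patients, with a stopping boundary of one-sided p < 0.0394 for harm or futility.

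**The concern.** The first trigger reads like a rule for a trial that treats a progressing disease. Here patients come for elective major abdominal surgery, and what is randomised is how fluids and vasoactive drugs are steered during the operation and for the first six hours after it. Harm that an investigator would suspect from this is an acute cardiac, pulmonary or renal event, not faster progression of the disease that led to surgery.

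If a site applies the printed rule to a life-threatening event that it attributes to the protocol, and the patient survives, it writes the event in the notes and the CRF. Nothing printed obliges it to tell the sponsor. At stake is whether the sponsor of a 15-centre trial without a safety committee learns of such events in time to act on them.

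**Working it through.** No figure in the plan needs reproducing, because the point rests on the text. The check sets the rules side by side and then asks how far the other safeguards fill the gap.

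**1. What each kind of event triggers (Adverse events section)**

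| Event | Notes and CRF | Report to sponsor | Time stated |
|---|---|---|---|
| Any adverse event, related or not | yes | none stated | none |
| Suspected faster progression due to the intervention | yes | yes | none of its own |
| Death judged caused by the intervention | yes | yes | immediate |
| Survived serious event attributed to the protocol, not a progression | yes | none stated | none |

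The last row is the gap. The immediacy sentence follows the sentence on deaths, so even the progression report has no clear time limit.

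**2. Does the progression trigger reach the last row?** It contains a causal element, because progression must be suspected to be due to the intervention. What must be caused, however, is progression of a disease or condition. An acute pulmonary oedema or kidney injury after surgery is a new event. A site could stretch the word condition to cover it, but then 15 centres may apply the rule differently.

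**3. Does the interim look stand in for reporting?** The rule is worded as a test of a hazard ratio and does not name its outcome. The only outcome that the article analyses by time-to-event methods is mortality (Kaplan-Meier, log rank, Cox).

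- If the look concerns mortality, it does not take in non-fatal events.
- If it is read as a comparison of complication proportions (an assumption), its power follows from

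 power = Φ((d − z·SE₀)/SE₁), with d = p_E − p_C, SE₀ = √(2p̄(1−p̄)/n), SE₁ = √((p_C(1−p_C) + p_E(1−p_E))/n).

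 Inputs: n = 50 per arm (half of 100), z = 1.758 for one-sided 0.0394, p_C = 0.28 from Sample size calculation, and p̄ the mean of the two rates.

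 At the printed planning rate p_E = 0.35: SE₀ = 0.0929 and SE₁ = 0.0926, so (0.07 − 0.1633)/0.0926 ≈ −1.01 and power is about 16%.

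 At p_E = 0.45: SE₀ = 0.0963 and SE₁ = 0.0948, so (0.17 − 0.1693)/0.0948 ≈ 0.01 and power is about 50%.

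 The same formula gives about 24% at 0.38, 70% at 0.50 and 94% at 0.60.

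Under either reading, the look is a single aggregate test. It does not bring an individual related event to the sponsor's attention.

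**4. Could a centre see a pattern alone?** With equal recruitment (assumed), 200/15 = 13.3 patients per centre, or 6.7 per arm. Take 7 per arm and an assumed 3–5% rate for a given serious event. The chance of seeing 0 or 1 in an arm is (1−r)⁷ + 7r(1−r)⁶, which is 0.98 at 3% and 0.96 at 5%. A single centre would almost never see a cluster.

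**The case against.** The strongest reply is that this is a condensed article. Trial status cites protocol version 2.0, which is not shown, and definitions and timelines for serious events are commonly kept in the full protocol. That is a fair answer to a complaint about silence. It does not answer this point fully, because the article is not silent: it prints a specific trigger, and that trigger is ill-suited. What stands is that a general serious-event procedure may exist elsewhere, in which case the two texts need to be reconciled.

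The second reply is that harm is captured: every adverse event reaches the CRF, the Table 1 events feed the primary outcome, and a look for harm is planned. This stands, and it rules out some stronger readings that a reader might infer:

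- **That non-fatal harm has no route at all, or that the sponsor cannot see it before the interim look.** Recording is complete, and nothing in the article says that CRF data are withheld from the sponsor. The sentence on deaths restricts which deaths are reported; it does not forbid reporting of other events. What is missing is a stated, timely report.
- **That the article itself attributes fluid overload to the protocols.** The Abstract and the Discussion mention overload only as something that titration by dynamic parameters avoids, and Table 1 assigns no complication to either protocol. That suspected harm would take the form of Table 1 events is a reviewer's inference from the nature of the intervention.
- **That the planning complication rates measure the number of events missed.** Those rates cover complications of any grade and any cause, most of which need no expedited report.

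**Conclusion.** The point holds as a badly chosen reporting rule. Of the two things named for report to the sponsor, the only one that can be non-fatal is tied to disease progression, which does not match the harm that a perioperative haemodynamic protocol could plausibly cause. A serious non-fatal event attributed to the protocol is recorded and may enter one aggregate look, but has no stated timely route to the sponsor.

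The article's reason for having no safety committee, that the protocols are known to be safe, does not close the gap: its Background says that only one trial has studied a protocol based on estimated oxygen extraction.

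The size cannot be given as a count, since the rate of serious, related, non-fatal events is not stated. The power and centre figures show only that the remaining safeguards are weak substitutes. They rest on the two-proportion reading of the interim rule, equal recruitment and an assumed 3–5% event rate. The conclusion itself rests on none of these, only on the printed reporting rules and the reading that an acute postoperative event is not disease progression. It is worth changing because the article says that recruitment was under way.

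**What to change.** In the Adverse events section, replace the progression trigger with a rule of this kind: any serious adverse event, fatal or non-fatal, that the investigator suspects is related to the haemodynamic protocol will be reported to the sponsor promptly, within a stated time limit. Align the sentence on deaths with it, so that fatal and non-fatal events do not use different thresholds of causality; the immediate report for deaths can stay. Expected surgical complications judged unrelated remain on the CRF only, which keeps the volume small.

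If the full protocol already contains such a rule, no new rule is needed, but the published section should be reconciled with it.

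The cost is one amendment and a small reporting burden for sites, which already record these events. Endpoints, sample size, treatment and the interim analysis are unchanged.

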### Sample size calculation

From literature analysis, we estimate a complication rate for control and experimental group of 28 and 35% respectively [2, 15]. With a non-inferiority margin of 10%, 184 patients (92 for each group) are needed to have a power of 80% and an alfa error of 0.05 [16]. Considering a 10% losing in follow-up, we enroll 200 patients (100 for each group).

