### Study design and setting

This is a multicenter randomized controlled trial. As both PGDT protocols showed to reduce postoperative complications compared to standard therapy and they are routinely applied for this kind of patients in common clinical practice [8, 12], a non-inferiority trial will be performed as the effect on primary outcome is expected to be maintained in both groups and it does not seem reasonable for ethical reason to deprive a study group of an established strategy for hemodynamic management during perioperative period. The study will be performed in 15 centers in Italy (Additional file 1).

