### Statistical analysis

Analysis will be performed on intention-to-treat basis.

Data will be checked for normal distribution using Kolmogorov-Smirnov test and presented as mean and standard deviation or as median and interquartile range as appropriate.

The primary end point is the difference of postoperative complication rate between the two group of patients. It will be evaluated using Fisher’s exact test or Pearson’s Chi square test as appropriate. Non-inferiority of experimental protocol respect to control group will be confirmed if the difference (including 95% confidence interval) will be lower than non-inferiority margin established at 10%. The 10% margin was chosen because it represents a two-thirds proportion of lower expected beneficial effect of PGDT (considering higher 95%CI for RR of 0.85) to reduce postoperative complications in comparison with conventional fluid therapy (RR 0.76 [CI95% 0.68–0.85]) [17].

Student t test or Mann–Whitney U test will be used to analyzed secondary outcomes as appropriate. Mortality between groups will be analyzed using the Kaplan-Meier method. The Log Rank test will be used to evaluate the statistical significance. Cox regression model using forward selection method for entering explanatory variables will be used to perform multivariate analysis. The age, type of surgery, ASA-PS classification and comorbidities will be considered as variables. A *p* value of F-test < 0.05 will be considered for variable inclusion. The amount of multicollinearity in the model will be estimated by the variance inflation factor (VIF). A VIF higher than 4 will be considered a sign of multicollinearity. Predicted R^2^ will be used to assess overfitting.

An interim analysis will be performed by independent statistician when 50% of information will be available (100 patients recruited). To monitor for harm or futility, the one-sided *p* value is calculated for testing the hypothesis HR = 1 versus the alternative HR > 1 (meaning the experimental treatment is doing worse than the standard treatment). If the *p* value is < 0.0394 at a monitoring time, then the trial would stop with the conclusion that non-inferiority cannot be claimed [18, 19]. Stopping rule for efficacy has not been defined [20].

For each statistical test, a *p* value < 0.05 is considered statistically significant.

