## Discussion

The role of perioperative hemodynamic optimization has been clearly shown by literature and the current spreading of mini-invasive monitoring systems able to estimate CO permits an easier application of these protocols than occurring in the past when only invasive techniques (e.g. pulmonary artery catheter) were available. As a predefined target of CO or DO_2_ seems to be not adequate for every patient, a personalized therapy is likely more appropriate. Following this concept, dynamic parameters of fluid-responsiveness (PPV and SVV) allow to titrate fluid administration aiming an increase of CO as a consequence of preload optimization but avoiding fluid overload. This approach has the advantage of personalized fluid therapy, but it does not consider if CO is adequate or not because preload optimization occurs independently from parameters of tissue perfusion and oxygen consumption. A protocol based on O_2_ER considers this second important aspect. An O_2_ER higher than a predefined cutoff is reflecting an inadequate DO_2_ to tissue and consequently an inadequate CO. This condition, but not fluid-responsiveness per se, is the trigger to start hemodynamic optimization. Moreover, in this contest we believe that CVP may be useful to limit fluid administration independently from PPV or SVV value. In fact, CVP depends on several conditions including preload status but also on cardiac function and ventricular compliance. Thus, this trial aims to demonstrate that this latest strategy of perioperative hemodynamic optimization is not inferior to the former in term of postoperative complications, but it may be responsible for a lower fluid administration. We decided to conduct a non-inferiority study because PGDT is routinely applied in this kind of patients due to the demonstrated benefits on outcome. Thus, small difference in reduction of postoperative complication rate between two different PDGT protocols seems reasonable.

Methodologically, the main limitation of this trial is the inability to blindly administer the interventions. However, this point is not clinically resolvable in this research field. Moreover, if participation of several centers may increase enrollment rate and may potentially extend the applicability of results, on the other hands too few patients per center may increases heterogeneity.

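### The sample size inputs cannot hold together: with 28% control, 35% experimental and a 10-point margin, 92 per group gives about 6 to 11% power, not 80%

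*Protocol article*

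**What the plan says.** All the planning inputs are printed in the protocol article, section Sample size calculation. On the rates: "we estimate a complication rate for control and experimental group of 28 and 35% respectively". On the size: "With a non-inferiority margin of 10%, 184 patients (92 for each group) are needed", with "a power of 80% and an alfa error of 0.05". The sidedness of alpha is not given. Enrolment is then set at 100 per group to allow for loss to follow-up.

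The section Statistical analysis fixes the endpoint and its direction: "The primary end point is the difference of postoperative complication rate between the two group of patients". Non-inferiority of the experimental protocol to control "will be confirmed if the difference (including 95% confidence interval) will be lower than non-inferiority margin established at 10" per cent. The endpoint is a complication rate, so higher is worse, and the quantity compared with the margin is experimental minus control.

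Nowhere does the article say that the experimental arm is expected to have fewer complications than control.

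**The concern.** A non-inferiority sample size depends on the distance between the assumed true difference and the margin. If the experimental arm is assumed to be 7 points worse and the margin is 10 points, the trial must exclude a 10-point excess when the true excess is 7. That takes thousands of patients per group, so a figure of 92 is not credible from those inputs.

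At stake is the stated basis of the primary conclusion. A reader who relies on 80% power believes that the trial is very likely to confirm non-inferiority under the printed rates. Under those rates it would almost always fail to do so.

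**Working it through.** **Inputs.** From Sample size calculation: control rate pC = 0.28, experimental rate pE = 0.35, margin M = 0.10, power 0.80, alpha 0.05 (sidedness unstated), 92 evaluable and 100 enrolled per group. From Statistical analysis: a 95% confidence interval for the difference, read here as two-sided, which is a one-sided test at 0.025.

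**Formula** (unpooled normal approximation, adverse binary outcome, 1:1 allocation):

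n per group = (z_alpha + z_power)² × [pC(1 − pC) + pE(1 − pE)] / [M − (pE − pC)]²

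The variance term is 0.28 × 0.72 + 0.35 × 0.65 = 0.2016 + 0.2275 = 0.4291. It does not change if the two rates are exchanged. The squared z sum is (1.645 + 0.842)² = 6.183 at one-sided 0.05 and (1.960 + 0.842)² = 7.849 at one-sided 0.025.

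**Reproducing the stated 92.** It needs a distance of 0.10 + 0.07 = 0.17, so that the experimental arm is 7 points better:

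- one-sided 0.05: 6.183 × 0.4291 / 0.0289 = 91.8, rounded up to 92, as stated
- one-sided 0.025: 7.849 × 0.4291 / 0.0289 = 116.5, rounded up to 117

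**Rates as printed.** The distance is 0.10 − 0.07 = 0.03:

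- one-sided 0.05: 6.183 × 0.4291 / 0.0009 = 2,947.7, rounded up to 2,948
- one-sided 0.025: 7.849 × 0.4291 / 0.0009 = 3,742.2, rounded up to 3,743

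**Other routes that keep the printed direction.** A continuity correction gives about 3,014 or 3,809 per group, and the Farrington-Manning variance about 2,940 or 3,732. An ordinary superiority comparison of 28% with 35% needs 544 to 719 per group. None comes near 92.

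**Power at the planned size**, from Φ{[M − (pE − pC)] / SE − z_alpha} with SE = √([pC(1 − pC) + pE(1 − pE)] / n). For the printed rates at n = 92, SE = √(0.4291 / 92) = 0.0683 and 0.03 / 0.0683 = 0.439. Subtracting 1.645 gives −1.206, which is 11.4%; subtracting 1.960 gives −1.521, which is 6.4%. The other cells follow in the same way:

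| True rates (control / experimental) | One-sided 0.05, n = 92 | One-sided 0.05, n = 100 | Two-sided 95% CI, n = 92 | Two-sided 95% CI, n = 100 |
|---|---|---|---|---|
| 28% / 35% (as printed) | 11.4% | 11.8% | 6.4% | 6.7% |
| 35% / 28% (reversed) | 80.1% | 82.9% | 70.2% | 73.7% |
| 28% / 28% | 44.7% | 47.2% | 32.7% | 35.0% |
| 35% / 35% | 41.2% | 43.6% | 29.5% | 31.7% |

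For the first two rows, simulation of the Wald interval rule (400,000 trials per cell) agrees with the formula to within half a percentage point; for the printed rates at 92 per group it gives 11.2% and 6.5%.

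**The case against.** The strongest reply is that this is a slip in one sentence: the two rates were printed in the wrong order and the calculation behind 92 is sound. That may be so, since 91.8 is a close match, but it is not established. The same 92 arises with the labels exactly as printed if a formula for a favourable outcome, where higher is better, was applied to complications. Then 28% and 35% are the intended assumptions and the sample size is what is wrong. The sources cited for the rates and the method are not at hand, so the documents cannot decide between the two.

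Nor does exchanging the labels restore 80% under the planned analysis. That figure belongs to one-sided 0.05; under a two-sided 95% interval the power is about 70% at 92 per group.

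A reader might also infer that the protocol contradicts itself by expecting equal complication rates. The documents do not support that. The remark in Study design and setting that "the effect on primary outcome is expected to be maintained in both groups" follows a comparison of both protocols with standard therapy, so it says that each keeps a benefit, not that the rates are equal. The Discussion's remark that "small difference in reduction of postoperative complication rate between two different PDGT protocols seems reasonable" justifies the non-inferiority approach and is not a planning assumption. Power under equal rates is therefore a useful sensitivity figure, not a figure that the protocol claims.

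Finally, one might fear that an inconclusive result would be read as inferiority. Nothing in the article invites that reading: it says only when non-inferiority will be confirmed or cannot be claimed. How to describe an interval that crosses the margin can be left to the analysis plan.

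**Conclusion.** The point stands as an error in the printed text. The rates, margin, power, alpha and sample size in Sample size calculation are mutually inconsistent, and no other section repairs them. As printed, the required size is about 2,948 or 3,743 per group, which is 32 or 41 times the stated 92 (2,948 / 92 = 32.0; 3,743 / 92 = 40.7). The design's power is about 11% or 6% at 92 per group and 12% or 7% at 100.

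The stated 92 rests on a 7-point advantage for the experimental arm and a one-sided 0.05 test. Whether transposed labels or a sign error led there is open.

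The conclusion assumes that the margin is an absolute difference in percentage points, as the decision rule implies, and that the 95% interval is two-sided. The first figure of each pair is for one-sided 0.05 and the second for the two-sided interval. The interim look is ignored; a stop for harm or futility could only lower the chance of confirming non-inferiority.

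**What to change.** First, state which complication rate belongs to which arm. Then restate the power under the 95% interval rule in Statistical analysis, using one alpha throughout the paragraph.

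- **If the labels were transposed** (control 35%, experimental 28%): correct the sentence, and say that the calculation assumes a 7-point advantage for the O2ERe protocol. Report power under a two-sided 95% interval of about 70% at 92 and 74% at 100 per group, and note that 80% at 92 per group holds only at one-sided 0.05.
- **If 28% control and 35% experimental are intended**: withdraw the 80% figure and report about 6 to 7% under the 95% interval rule.
- **In either case**: add the power under equal rates of 28% or 35% as a sensitivity figure, about 30 to 35% at 92 to 100 per group with the 95% interval.

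The cost is a rewritten paragraph and a less favourable power statement. No extra patients are requested.

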### Randomization

After screening for inclusion and exclusion criteria, patients suitable to be enrolled will be allocated with 1:1 ratio to randomly receive one of the two protocol of perioperative hemodynamic optimization. A computer-based system will be used to create a block randomization list (block size of 6). The allocation sequence concealment will be guaranteed by sealed opaque envelopes. Patients and researchers that perform postoperative follow up will be blinded to the allocated protocol.

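### The stated 80% power does not belong to the 95% CI decision rule: even with the written rates reversed in the new protocol's favour it is about 69–74%, and with the rates as written about 6%

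*Protocol article*

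**What the plan says.** All of these statements are in the Protocol article.

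- **Assumed rates (Sample size calculation):** "we estimate a complication rate for control and experimental group of 28 and 35% respectively". As written, the experimental arm is 7 points worse.
- **Margin, power and error (same section):** with a margin of 10 points, "184 patients (92 for each group) are needed to have a power of 80% and an alfa error of 0.05". No side is given for the 0.05.
- **Loss allowance (same section):** "Considering a 10% losing in follow-up, we enroll 200 patients (100 for each group").
- **Decision rule (Statistical analysis):** non-inferiority "will be confirmed if the difference (including 95% confidence interval) will be lower than non-inferiority margin established at 10" per cent. Whether the interval is two-sided is not stated. The same paragraph supports the margin with an ordinary two-sided 95% interval for a relative risk, 0.68 to 0.85.
- **Allocation and population:** "patients suitable to be enrolled will be allocated with 1:1 ratio" (Randomization), and "Analysis will be performed on intention-to-treat basis" (Statistical analysis).

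The endpoint is a complication rate, so a higher value is worse and non-inferiority depends on the upper confidence limit of experimental minus control.

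**The concern.** A power statement is meaningful only for the test that will be applied and for the rates assumed. Here the sample size appears to rest on one error level and the decision on a stricter one. The only direction of effect that yields the stated number is also the opposite of the direction printed beside it. If so, the 80% describes neither the planned decision rule nor the planned assumption.

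Two things are at stake. First, the chance of an inconclusive trial is larger than readers, ethics committees and sites have been told. Second, a result whose 90% interval clears the margin while its 95% interval does not would be open to dispute, because the sample size section could be cited afterwards for the looser level.

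**Working it through.** **Inputs.** Rates 28% and 35%, margin 10 points, power 80%, alpha 0.05, 1:1 allocation, 200 enrolled, 10% loss (Sample size calculation and Randomization); 95% CI (Statistical analysis). The unpooled variance term is 0.28×0.72 + 0.35×0.65 = 0.2016 + 0.2275 = 0.4291, the same whichever arm has which rate.

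**1. Reproducing 92 per group.** The formula is n = 0.4291 × (z_α + z_β)² / d², where d is the distance from the assumed difference to the margin.

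- Favourable direction (35% control, 28% experimental): d = 10 + 7 = 17 points. With one-sided 5%, n = 0.4291 × (1.645 + 0.842)² / 0.17² = 91.8, so **92**, the plan's figure.
- Same direction, one-sided 2.5%: n = 0.4291 × (1.960 + 0.842)² / 0.17² = 116.5, so 117.
- Rates as written (28% control, 35% experimental): d = 10 − 7 = 3 points. n = 2,948 at one-sided 5% and 3,743 at one-sided 2.5%.
- No true difference (both arms at 28%, 31.5% or 35%): n = 250 to 282 at one-sided 5%, 317 to 358 at one-sided 2.5%.
- A superiority comparison of 28% with 35%: n = 691 two-sided, 544 one-sided, 719 with continuity correction.

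Of these variants only the first gives 92. It needs both the one-sided 5% error and the reversed rates.

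**2. Power under the stated decision rule.** Power = Φ(d / √(0.4291/n) − z). For example, with d = 0.17, n = 92 and z = 1.960: √(0.4291/92) = 0.0683; 0.17/0.0683 = 2.489; 2.489 − 1.960 = 0.529; Φ(0.529) = 0.702.

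| Per group | Favourable, one-sided 5% | Favourable, two-sided 95% CI | As written, two-sided 95% CI |
|---|---|---|---|
| 90 (200 less 10%) | 79.3% | 69.2% | 6.4% |
| 92 (as stated) | 80.1% | 70.2% | 6.4% |
| 100 (no loss) | 82.9% | 73.7% | 6.7% |

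Exact binomial enumeration of the Wald interval rule agrees. For 90, 92 and 100 per group under the two-sided 95% CI it gives 69.4%, 70.3% and 74.1% in the favourable direction, and 6.5%, 6.5% and 6.9% as written. With the rates as written, even one-sided 5% gives only about 11 to 12%.

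**3. Size needed for 80% under the 95% CI, favourable direction.** 117 per group, or 234 evaluable; 117/0.90 = 130 per group, or 260 enrolled.

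**4. Loss allowance.** 200 × 0.90 = 180, which is below 184. The correct inflation is 184/0.90 = 204.4, so 205, or 206 for equal arms (92/0.90 = 102.2, so 103 each). Even the cruder 184 × 1.10 = 202.4 exceeds 200. The loss that 200 does cover is 1 − 184/200 = 8%.

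**5. Separating the two effects.** At 92 per group, moving from one-sided 5% to the two-sided 95% CI takes power from 80.1% to 70.2%, about 10 points. Falling from 92 to 90 per group takes it from 70.2% to 69.2%, about 1 point.

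**The case against.** The best counter-argument is that neither section states a side. Only the upper limit matters here. If the 95% interval was meant as a one-sided bound, the two sections agree and power in the favourable direction is 79–80%. That is possible, and the one-sided 5% in the sample size is itself an inference from reproducing 92, not something the article declares. But nothing in the text signals a one-sided bound, and the same paragraph uses a 95% interval in the two-sided sense. The general 0.05 significance threshold that closes the analysis section does not settle the side either. So the point stands as a stated power that the usual reading of the stated rule does not deliver.

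Several stronger readings are tempting and are not supported:

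- *The trial has 69% power.* That figure holds only for 35% control and 28% experimental, the reverse of the printed rates. Putting it beside the rates as they stand would introduce a new error.
- *The type II error is about 30% in any case.* In the favourable direction with all 200 analysed it is about 26%. The endpoint covers the hospital stay and the analysis is by intention to treat, so actual loss may be below 10%; at 8% or less, 184 is met.
- *The loss sentence is a main cause of the shortfall.* It accounts for about 1 point.
- *The mismatch raises the risk of wrongly declaring non-inferiority.* It does not, provided the two-sided 95% interval is applied, because that is the stricter rule.

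**Conclusion.** The concern holds in a limited form. The error level, the confidence level and the direction of the assumed rates do not fit together, and the stated 80% is not the power of the stated decision rule under either direction. With the two-sided 95% interval, power is about 69% to 74% if the assumption is 35% control and 28% experimental, and about 6% if it is 28% control and 35% experimental as written. The loss allowance is arithmetically wrong but minor.

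This rests on three assumptions: the interval is two-sided, the variance is unpooled (which reproduces the plan's figure), and the margin is an absolute 10 points. The document does not show which direction of rates was intended. The reproduction of 92 shows which one was used in the calculation, and no more than that.

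**What to change.** Make these changes together, before the interim analysis:

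1. Keep the 95% CI rule, say that it is two-sided, and state the error in the sample size section as one-sided 0.025.
2. Reconcile the direction of the assumed rates in the same edit, saying explicitly which rate belongs to which arm.
3. Restate power for the rates finally given. About 69% after 10% loss, or 74% with all 200 analysed, may be written only if those rates are 35% control and 28% experimental.
4. Alternatively, if one-sided 5% was intended, name a 90% two-sided interval (a one-sided 95% bound) in the analysis section. Power in the favourable direction is then about 79% after 10% loss.
5. Correct the loss sentence: either 200 patients allow for 8% loss, or 206 are enrolled to allow for 10%.

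The cost is wording and, under the 95% rule, a less favourable stated power. Enrolling 206 would add 6 patients. Restoring 80% under the 95% rule in the favourable direction would be a larger step: 260 enrolled, 60 more than planned.
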